#### Missing data and sensitivity analysis

In order to obtain the complete dataset, the researchers will receive professional training to avoid missing data. Experienced investigators will contact participants through messaging and telephone calls at fixed treatment periods. In addition, the participants will receive economic compensation after the trial. For missing data, we will analyze the underlying reason and use an imputation adjustment approach. The method of last observation carried forward (LOCF) will be carried out for imputation of missing values. After the main analysis, sensitivity analysis of the various datasets will be used to evaluate the impact of missing data on the trial results.

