### Outcome measurements

#### Primary outcome measurement

##### Neck Pain Scale

The Northwick Park Neck Pain Questionnaire (NPQ) has been widely used in research and has been shown to have high validity and reliability for neck pain measurement [22]. It is comprised of nine items including the degree and duration of pain, symptoms including numbness, sleep and social activities, and quality of life aspects. The highest score is 100 and high scores indicate severe damage due to neck pain. The NPQ will be completed after each treatment and in the follow-up period.

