#### Follow-up

The researcher will contact the patients via telephone and a short messaging service. The follow-up period will be 3 months and monthly information will be collected. If participants discontinue the intervention protocols, the latest outcome data including changes in symptoms and medication compliance will be presented. The reasons for treatment failure will be recorded and analyzed.

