#### Statistical analysis

A statistical analysis will be performed using the Statistical Package for Social Sciences (SPSS, version 16.0, SPSS Inc., Chicago, IL, USA) in the Center of Acupuncture Clinical Research. A full analysis set (FAS) will be performed as the main analysis. According to the principle of intention-to-treat (ITT), any participants who randomly receive at least one treatment should be included in the main analysis dataset. The per-protocol (PP) set as the subset of FAS will include subjects who complete the study and have main variable baseline values in this trial. To be included in the safety set, patients will receive at least one safety evaluation after treatment. Statistical analysis of the main parameters will be carried out at baseline, at each visit and in the follow-up period. Frequency tables and charts will be used to analyze completed AE questionnaires.

Descriptive statistics will be performed to compare baseline information, patient characteristics and an evaluation of the credibility of the five groups. To determine the primary and secondary outcomes, the mean differences from baseline to the end of follow-up period will be compared and analyzed. Group differences for continuous variables will be analyzed using analysis of variance (ANOVA) to compare the subjective and semi-objective outcomes. The Wilcoxon rank sum test will be used to compare the outcome measurements before and after treatment. The differences in categorical variables between groups and adverse effects will be analyzed using the chi-square test. A *P* value of 0.05 or less will be considered significant.

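### LOCF is fixed for missing NPQ scores although the score is expected to move and the comparison runs to 3 months, so unequal dropout would bias the arm difference

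*Protocol article*

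**What the plan says.** Under Missing data and sensitivity analysis, the protocol article states: "The method of last observation carried forward (LOCF) will be carried out for imputation of missing values". It names no other imputation method. It adds that, after the main analysis, "sensitivity analysis of the various datasets will be used to evaluate the impact of missing data on the trial results".

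Under Statistical analysis, "A full analysis set (FAS) will be performed as the main analysis". By appeal to intention-to-treat, "any participants who randomly receive at least one treatment should be included in the main analysis dataset". The per-protocol set, a subset of this, "will include subjects who complete the study and have main variable baseline values in this trial". For the outcomes, "the mean differences from baseline to the end of follow-up period will be compared and analyzed".

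On data collection, Neck Pain Scale says: "The NPQ will be completed after each treatment and in the follow-up period". Follow-up says: "The follow-up period will be 3 months and monthly information will be collected". Sample size calculation takes mean NPQ changes of 20.71 (SD 11.91) and 24.04 (SD 11.83) as expected values and allows for up to 15% dropout.

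**The concern.** LOCF is unbiased for a patient only if the score would have stayed where it was last seen. The plan expects otherwise: NPQ should shift by more than 20 points, over ten sessions in 5 weeks, followed by 3 months without study treatment.

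- A patient who leaves mid-course is credited with part of the effect.
- A patient lost after week 5 has the end-of-treatment score entered as the 3-month result.
- Single imputation counts filled-in scores as measured ones, so the uncertainty they carry is ignored.

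Equal errors in all arms largely cancel in the comparison. Unequal ones do not. Unequal dropout is conceivable here: Background and Discussion cite reports that about 40% to nearly half of subjects could tell the non-penetrating needle from real treatment, and group E receives that needle. The article gives no dropout figures by arm, so this is a plausible route and not a documented one.

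At stake is whether a modest between-arm difference on the primary outcome reflects needling or the pattern of dropout.

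**Working it through.** **Inputs from the protocol article.** Mean NPQ changes 20.71 and 24.04, SDs 11.91 and 11.83, dropout allowance 15%, 35 per arm (Sample size calculation); ten sessions (Interventions). The planning difference is 24.04 − 20.71 = 3.33 points. The plan gives no estimate of missing-data bias to reproduce.

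**Assumptions, not in the documents.** The 20.71-point change is an improvement, the same in both arms compared. It accrues linearly over ten sessions and is then held. Dropout is spread evenly over sessions 1 to 9 and is unrelated to outcome. The dropout shares by arm are illustrative.

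**Formula.** Bias in the arm difference = q₁b₁ − q₂b₂, where q is an arm's dropout share and b the mean error of the carried score among its dropouts.

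**Mean carry error.** A patient last seen after session k falls short by 20.71 × (1 − k/10). The average of (1 − k/10) over k = 1 to 9 is (9 − 4.5)/9 = 0.5, so b = 0.5 × 20.71 = 10.36 points.

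**Bias with equal b in both arms.**

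| Dropout | Calculation | Bias (points) | Share of 3.33 |
|---|---|---|---|
| 15% v 15% | 0 × 10.36 | 0 | 0% |
| 15% v 5% | 0.10 × 10.36 | 1.04 | 31% |
| 15% v 0% | 0.15 × 10.36 | 1.55 | 47% |
| 25% v 5% | 0.20 × 10.36 | 2.07 | 62% |

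The last row puts one arm above 15%, although the two arms average 15%.

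**Equal dropout, unequal carry error.** With 15% lost in each arm and mean errors differing by 5 or 10 points, for example through different timing, the bias is 0.15 × 5 = 0.75 or 0.15 × 10 = 1.5 points (23% or 45% of 3.33).

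**What it takes to reach 3.33.**

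- Dropout spread over sessions 1 to 9 needs a gap of 3.33/10.36 = 32 percentage points.
- If all dropouts leave after session 1, b = 0.9 × 20.71 = 18.64, and 25% v 5% gives 0.20 × 18.64 = 3.73. After session 2, b = 0.8 × 20.71 = 16.57, giving 3.31.
- At 15% v 0%, losing the entire change gives 0.15 × 20.71 = 3.11, or 0.15 × 24.04 = 3.61.
- At 15% in both arms, the mean carry errors must differ by 3.33/0.15 = 22.2 points.

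**Scale against sampling error.** With a pooled SD of √((11.91² + 11.83²)/2) = 11.87, the standard error of a pairwise difference at 35 per arm is 11.87 × √(2/35) = 2.84. Biases of 1.04 to 2.07 are 0.37 to 0.73 of that.

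**Loss after week 5.** The article gives no expected drift after treatment, so this part cannot be sized. If scores worsen after treatment, the carried value is too favourable, which is the opposite error from mid-course dropout.

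**The planned check.** In the scenario above, completers show no arm difference, while the full analysis set with LOCF shows up to 2.07 points. The two analyses would disagree.

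**The case against.** Several points on the other side stand.

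- A reader might infer that dropout could readily produce a spurious difference as large as the planned one. The figures do not support that. If no arm exceeds 15%, the linear model gives at most 1.55 points, and 3.33 needs early and strongly unbalanced dropout.
- A reader might also infer that no planned check would reveal the problem. That is wrong: completers and the full analysis set rest on different assumptions and can disagree visibly. But a disagreement does not say which result is right, and agreement is not reassuring when dropout depends on outcome, because both may then be biased.
- With equal 15% dropout, each arm's mean change is understated by 0.15 × 10.36 = 1.55 points, but that is within arm. A true 3.33-point difference would shrink by only 0.15 × 0.5 × 3.33 = 0.25 points.
- Mid-course and post-treatment carry errors may partly offset each other. How far is unknown.
- The plan records reasons for withdrawal, analyses the dropout rate and looks into reasons for missing data (Data monitoring and quality control; Follow-up; Missing data and sensitivity analysis). These steps help interpretation but do not correct a main estimate built on LOCF.
- The article is condensed, and a full protocol or analysis plan may specify more sensitivity analyses. That would not undo the choice of LOCF, which the article states outright.

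Excluding randomised but untreated patients is a lesser matter. The article gives no count of them, and none of the arithmetic rests on them. Only the acupuncturists know the allocation (Blinding), and patients are not told their treatment type, so a large effect should not be inferred.

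**Conclusion.** The concern holds as a stated and inferior choice of method that should be changed. LOCF does not fit an outcome expected to move by more than 20 points and compared at the end of a 3-month follow-up. Under the assumed linear course, its bias is a material fraction of the planning difference when dropout is unbalanced: 31% at 15% v 5%, 47% at 15% v 0% and 62% at 25% v 5%. It is zero when dropout and carry error are equal, and the full 3.33 points is a limiting case.

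The direction and actual size cannot be known from the document, because it gives no dropout by arm, time course or post-treatment drift. The 3.33 points serve only as a yardstick, and the case against LOCF does not depend on them. The planned contrast of datasets is a partial warning, and it does not probe outcome-dependent dropout. Calling a set restricted to patients with at least one treatment intention-to-treat is inaccurate, but secondary.

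**What to change.** 1. **Primary analysis.** Use a likelihood-based repeated-measures model on the scheduled NPQ scores, with arm, visit, arm-by-visit interaction and baseline NPQ, and take the 3-month contrast as the estimate. Multiple imputation followed by ANCOVA at 3 months is an acceptable alternative.
2. **LOCF.** Report it as a secondary result at most.
3. **Sensitivity analysis.** Add a delta-adjusted or reference-based imputation (for instance with group E as reference), so that the missing-data assumption varies and not only the dataset.
4. **Analysis set.** Include all randomised patients as randomised, or stop describing the at-least-one-treatment set as intention-to-treat. Patients with no NPQ score after baseline add nothing to a model that uses baseline as a covariate, so the imputation-based analyses should cover them.

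The cost is revised wording and modest programming. NPQ is already collected repeatedly, so no new data or visits are needed. With about 35 patients per arm and many visits, the covariance structure must be specified in advance. Confidence intervals will probably be slightly wider than LOCF would report. The change should be fixed before data lock, while the statistician is still blinded.

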#### Ethical considerations

This research was designed in accordance with the principles of the Declaration of Helsinki. The trial protocol has been approved by the Ethics Committee of Guangdong Provincial Hospital of Chinese Medicine (Reference number B2015-058-01), and is registered on the primary registry in the World Health Organization (WHO) registry network (Chinese Clinical Trial Registry: No. ChiCTR-IOR-15006886). Signed consent will be obtained from each patient after they are informed of the procedures, possible risks of the trial and their right to discontinue participation. In addition, for those who develop several AEs, the Ethics Committee will be informed and medical treatment will be provided until the problem is resolved.

#### Monitoring and publications

An independent board from the Center of Acupuncture Clinical Research will monitor progression and provide advice when necessary. The Data Monitoring Committee has been established independently in the hospital (Traditional Chinese Medicine Hospital of Guangdong Province) and has claimed that there is no conflict of interest.

This RCT protocol was developed following the Standard Protocol Items: Recommendations for Interventional Trials (SPIRIT) Checklist (see Additional file 1) [27]. We plan to publish the protocol and results according to the guidelines of Consolidated Standards of Reporting Trials (CONSORT) and Revised Standards for Reporting Interventions in Clinical Trials of Acupuncture (STRICTA) [28, 29]. All staff who participated in the study will be included in the authorship and in the “Competing interests” statement.

## Discussion

Acupuncture has been practiced for more than two millennia in China. In the practice of traditional acupuncture analgesia, it is generally acknowledged that structures and physiological functions are modulated by 14 energy meridians and the hypothetical “Qi” is usually translated as energy [30]. Acupuncturists with different experiences might have the different methods to operate *de-qi* (bring about the desired sensation) for the acupuncture intervention. Findings from clinical research strongly suggested that these specific differences of interventions have a major impact on the response to the curative effect [31]. Therefore, further trials are required to investigate the differences in these methods.

According to TCM theory, acupoints can be selected in three ways: an acupoint can be selected at a local lesion (with the pain area as acupoint *Shu*), far away from the local lesions, such as on limbs, and in accordance with symptoms. For non-acupoints at local lesions, the possible mechanisms of the analgesic effect may include the gate control theory triggered by neural pathways, alterations in local circulation and the immune environment [32]. Moreover, for shallow needle insertion, some researchers believe that shallow puncture can stimulate afferent nerves and activate the corresponding brain regions to produce a “limbic touch response” [33, 34]. Previous studies have also suggested that non-acupoints beyond the meridian and shallow puncture have an analgesic effect in subjects with fibromyalgia and other chronic pain conditions [35, 36]. Although the use of the “Streitberger” needle with a blunt tip has been supported in studies and reviews, it was reported that nearly half of the subjects could distinguish it from the real treatment in pain disorders [14, 37]. Therefore, further trials are required to investigate these differences. It is necessary to establish a standard for the control (sham) in clinical research due to the unknown analgesia mechanisms of traditional acupuncture.

Clinical trials of traditional acupuncture for chronic pain, with optimal control groups, are rare, with the exception of the use of standard outcome measures and rigorous blinding of participants to treatment assignment [38]. However, few guidelines exist for conducting appropriate sham acupuncture, for the depth of the inserted needle or the parameter for needle stimulus [39, 40]. This randomized placebo-controlled trial addresses the urgent need to provide evidence-based control groups for adults with CNP and to determine the evidence for the specificity of acupoints. At the end of this clinical trial, we expect that the findings will provide evidence to answer the question: is acupuncture more effective than a placebo?

### Trial status

The participants are beginning to be recruited for this study. The trial is designed to be completed by 31 December 2017.

## Abbreviations

AEs: Adverse events
ANOVA: Analysis of variance
BI: Blinding index
CNP: Chronic neck pain
CONSORT: Consolidated Standards of Reporting Trials
CRF: Case Report Form
FAS: Full analysis set
ITT: Intention-to-treat
LOCF: Last observation carried forward
NPQ: Northwick Park Neck Pain Questionnaire
PP: Per-protocol
PT: pain threshold
SD: Standard deviation
SF-36: Short-form 36-Item Health Survey
SF-MPQ-2: Short Form McGill Pain Questionnaire-2
STRICTA: Revised Standards for Reporting Interventions in Clinical Trials of Acupuncture
TCM: Traditional Chinese medicine
VAS: Visual Analogue Scale
